#### Sample size estimation

Sample size calculation was performed based on *BMAL1* gene expression data from our previous work [34] assuming that all measurements follow a sinusoidal wave function $y_{i}=A\;sin\;(\omega (t_{i}+\phi ))+M+\varepsilon_{i}$, 1 ≤ i ≤ n whereby n is the total number of samples, $\omega =\frac{2\pi }{Period}$ the frequency of the sinusoidal wave, φ the phase shift, M the rhythm-adjusted mean (MESOR), and t_i_ the observed Zeitgeber time. ε_i_ is the error term for sample i. We assume ε_i_ are identically and independently distributed from $\varepsilon_{i}∼N(0,\sigma^{2})$, where σ is the noise level. The null hypothesis that there is no circadian rhythmicity (H_0_ = 0) is tested against the alternative hypothesis that a circadian rhythmicity pattern exists (H_A_≠0). Rhythmicity will be tested using the F-test which compares the fitted model against a restricted model. For details see please Cornelissen [39]. The study is considered successful if rhythmicity is detected in the measured core-clock and clock-controlled genes obtained from saliva samples. To account for multiple comparisons (comparisons between gender and age subgroups and various seasons, in total up to 10 comparisons) the type I error is set to 0.005 according to the Bonferroni correction to hold the global significance level of α = 0.05. Underlying the data of our previous study [34], an amplitude (A) of 1.11 is estimated for *BMAL1* gene expression and the standard deviation of residuals (s) is 1.36, which gives an estimate of the intrinsic effect height of r = A/s = 0.82.

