In order to detect an intrinsic effect of r = 0.82 as significant at α = 0.005 and achieve a power of 0.8, a sample size of 52 is necessary (**Fig 2**). The sample size was estimated by R package CircaPower [40]. A dropout rate of 10–15% [41–44] is generally considered for calculating the sample size in clinical studies although there is no universal filter. As a compromise for potential higher dropout due to the longitudinal design of our study, we considered a dropout of 12% in our sample size estimation, and calculated a population of 59 participants to be sufficient to allow for the planned comparisons in the subset of a) females vs males or b) age groups or c) seasons. Participants will be distributed evenly for comparisons (e.g., for sample size) or appropriate statistical measures will be taken, by using statistical tests considering unequal sample size. Participants for whom there are no saliva samples collected are considered as dropout.

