### Participant recruitment

Participants will be recruited among the physically active, healthy individuals who volunteer to participate in the study and meet the inclusion criteria. Participants will be asked for their health status at the time of recruitment, which is the state of physical, mental and social well-being and not merely the absence of a chronic disease according to the definition by WHO (World Health Organization) [45]. In this study heart or respiratory diseases such as hypertension or sinusitis were not used as an exclusion criterion if participants went through treatment and were able to maintain a physically active life. For recruitment, announcements with approved flyers were distributed via the BTSC (Berlin Turn and Sports Club). Participants that are part of BTSC are either amateur or professional athletes. Participants who are not members of the sports club, will be asked whether they participate in physical activities according to the WHO definition, which includes activities such as walking, cycling, sports or active recreation and play [46].

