#### Analysis for secondary endpoints

Differences in CR and mean gene expression level between subgroups, with respect to sex, age, seasons and physical performance, will be evaluated by CircaCompare [57] to estimate and observe differences between CR, specific to the characteristic desired (mesor, amplitude and phase). The methodology proposed by Parsons *et al*. [57] will be used for exploratory purposes, and circadian curves will be estimated per individual and sampling round. Additionally, correlations between molecular data and physical exercise measurements, as well as for hormonal data (melatonin and cortisol) and activity data (smart-tracker) will be calculated.

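### The stated answer to uneven groups covers group size, not composition, so the sex and age contrasts in the rhythm could confound each other

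*Protocol article*

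**What the plan says.** - **Sample size estimation.** The total is held to be enough for comparing females with males, or age groups, or seasons. Participants are to be spread evenly over the comparisons, with sample size given as an example; failing that, "appropriate statistical measures will be taken, by using statistical tests considering unequal sample size". The calculation itself concerns detection of a rhythm: "Rhythmicity will be tested using the F-test which compares the fitted model against a restricted model", and "the type I error is set to 0.005 according to the Bonferroni correction".
- **Analysis for primary endpoint.** Mesor, amplitude and phase are estimated by cosinor regression for each gene in the sex, age and season subgroups.
- **Analysis for secondary endpoints.** "Differences in CR and mean gene expression level between subgroups, with respect to sex, age, seasons and physical performance" are evaluated by CircaCompare. Curves per individual and sampling round are also planned. Neither analysis section names a covariate or a model holding sex and age together.
- **Introduction.** Females tend to peak earlier than males, and ageing may advance phase and dampen amplitude.
- **Participant recruitment.** Volunteers come through a sports club or from outside it. "Participants that are part of BTSC are either amateur or professional athletes"; non-members are asked whether they are physically active by the WHO definition.
- **Digital questionnaires.** Activity scores are collected to categorise participants and perhaps to correlate with expression, not to adjust the sex or age contrasts.

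**The concern.** The compared groups are self-selected volunteers. Equal numbers of men and women can still have different age mixes, and age groups of equal size can still differ in the share of women. A test that allows for unequal numbers gives a valid standard error for the difference between two groups. It does not change what that difference estimates. If one sex is older on average, an unadjusted sex contrast in phase or amplitude contains part of the age effect, and the reverse holds for the age contrast.

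The Introduction gives the direction. If the women are older than the men, an earlier phase from age adds to any female advance; if the men are older, it hides some of it. At stake is how the sex and age profiles are read. They form part of the primary objective and, by the Discussion, may later serve as a healthy reference for disease comparisons.

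**Working it through.** **1. The plan's own figure.** Inputs from Sample size estimation: "an amplitude (A) of 1.11 is estimated for" *BMAL1*, "the standard deviation of residuals (s) is 1.36", giving an "intrinsic effect height of r = A/s = 0.82" (1.11/1.36 = 0.816). For a cosinor F-test with 2 and n − 3 degrees of freedom and evenly spaced sampling times, the noncentrality is n·r²/2. At n = 52 this is 52 × 0.6724 / 2 = 17.48, and power at 0.005 is 0.8002. So 52 is reproduced (53 with unrounded r). Dropout: 52/0.88 = 59.09, stated as 59. This is the size for one test of whether a rhythm exists. It says nothing about the composition of the groups to be compared.

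**2. The bias.** Let p_F,k and p_M,k be the shares of females and males in age group k, and μ_k the mean of a rhythm parameter in that age group. With no true sex effect, the unadjusted sex contrast has expectation Σ_k (p_F,k − p_M,k)·μ_k. With two age groups that differ by δ it is (p_F − p_M)·δ. This is exact for averages of per-person parameters and approximate for the phase of a pooled curve. Group sizes do not enter.

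**3. In hours of phase.** The article gives neither δ nor the mix, so both are assumed. Take δ = 1–2 h between teenagers and older adults, with only those two groups present:
- equal mix: 0 h
- 50% against 25% teenagers: 0.25 × (1 to 2) = 0.25–0.5 h
- 60% against 20%: 0.40 × (1 to 2) = 0.4–0.8 h

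Leaving out the young adults sharpens the contrast, so the last line is towards the severe end.

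**4. Does an unequal-size test help?** Simulation with no true sex effect: a per-person rhythm parameter with SD 1 within age group, an age effect of 0.5–1.0 SD, a Welch test at 0.005 and 20,000 runs per setting. All these inputs are assumed; the total of 52 is the plan's.

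| Sex groups | Difference in share of older participants | Bias (SD) | False positives (nominal 0.5%) |
|---|---|---|---|
| 26/26 | 0 | 0 | about 0.5% |
| 35/17 | 0 | 0 | about 0.5% |
| 26/26 | 0.2 | 0.10–0.20 | 0.7–1.5% |
| 35/17 | 0.2 | 0.10–0.20 | 0.7–1.5% |
| 26/26 | 0.4 | 0.20–0.40 | 1.8–6.3% |
| 35/17 | 0.4 | 0.20–0.40 | 1.4–5.4% |

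When only the sizes differ, the test holds its level. When the age mix differs, it does not, even with equal groups.

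**5. Does adjustment help?** With age group in a linear model, checked at a 0.4 difference in share (4,000 runs per setting), the bias is 0.004–0.007 SD and the false-positive rate 0.4–0.5%.

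**The case against.** The strongest reply is that this is a condensed article. Covariates for secondary comparisons are usually set in an analysis plan, and none is shown here. The quoted clause also sits under sample size and does not claim to control confounding. That stands as far as it goes: the absence of covariates alone would be no finding. But the article does state what will be done when groups are not even, and does name the method for the contrasts. Followed as written, these leave a difference in composition untouched.

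A reader might infer more than the article supports:
- **That the unequal-size test is the only remedy.** Even distribution comes first in the same sentence, and sample size is only its example. It could extend to composition, but nothing says that it does.
- **That the contrasts will be biased.** Confounding also needs sex and age to be associated in the sample, and no recruitment figures are given.
- **That athlete status is a confounder of the same standing.** The article says the clock influences performance, and that mean *BMAL1* expression correlates with muscle tone in active people. It does not say that club membership shifts the rhythm, and club members include amateurs.
- **That season contrasts share the problem.** Four rounds per person across both seasons make them largely within person.
- **That joint modelling is excluded.** The article never says the factors are analysed strictly separately, and per-person curves leave adjustment open.

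The success criterion, detection of rhythmicity, is not affected.

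**Conclusion.** The point holds in a conditional form. Neither even distribution as described nor a test for unequal sizes secures equal composition, and the stated contrasts have no joint model. If the age mix differs between the sexes, or the sex mix between age groups, the contrasts in mesor, amplitude and phase could be confounded, because by the article's own account both factors can affect the rhythm.

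The size cannot be fixed from the article. Under the assumptions above, it runs from nothing with equal mixes to 0.25–0.5 h of spurious phase difference for a 25-point difference in age mix, and 0.4–0.8 h for 40 points. False positives at a nominal 0.5% rise to 0.7–6.3% over the assumed range with equal group sizes. The change is worth making because the group comparisons carry much of the study's interpretation and the variables needed are already recorded.

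**What to change.** In Sample size estimation and in Analysis for secondary endpoints, state the following:

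1. Sex and age-group differences in mesor, amplitude and phase will be estimated in one cosinor model, or from per-person cosinor parameters, with sex adjusted for age group and age group adjusted for sex.
2. The sex-by-age composition of the analysed sample will be reported.
3. Recruitment source (club member, yes or no) and the physical-activity questionnaire score will be added as covariates in a sensitivity analysis only.

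A test that allows unequal sizes may stay, but not as the answer to groups that differ in composition. Season contrasts need no such adjustment. Watching recruitment by sex within age group is optional: 59/6 is about ten people per cell, and recruitment began in May 2022 and is to end with 2023.

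**Cost.** No new data or visits are needed. In a joint cosinor model each added contrast takes three parameters (mesor, cosine and sine). Adjusting sex for three age groups therefore adds 2 × 3 = 6 per gene, and adjusting age group for sex adds 3. With per-person parameters the cost is two degrees of freedom or one for each parameter analysed. Intervals become slightly wider.

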**Fig 2 pone.0293226.g002:**
[figure not shown]
Graphical illustration of sample size estimation for the study protocol. The plot illustrates the identification of CR parameters based on *BMAL1* gene expression, which is then used to determine of sample size values and corresponding test power. Dashed red line indicates the optimal sample size (N) that needs to be collected for the detection of significant results according to pre-determined thresholds (α = 0.005; power = 0.8; r = 0.82). Accordingly, by considering a dropout rate of 12% a sample size of 59 participants was determined as needed to successfully assess the null hypothesis.

### Participant recruitment

Participants will be recruited among the physically active, healthy individuals who volunteer to participate in the study and meet the inclusion criteria. Participants will be asked for their health status at the time of recruitment, which is the state of physical, mental and social well-being and not merely the absence of a chronic disease according to the definition by WHO (World Health Organization) [45]. In this study heart or respiratory diseases such as hypertension or sinusitis were not used as an exclusion criterion if participants went through treatment and were able to maintain a physically active life. For recruitment, announcements with approved flyers were distributed via the BTSC (Berlin Turn and Sports Club). Participants that are part of BTSC are either amateur or professional athletes. Participants who are not members of the sports club, will be asked whether they participate in physical activities according to the WHO definition, which includes activities such as walking, cycling, sports or active recreation and play [46].

#### Inclusion criteria

1) The consent form must be signed before study-specific tests or procedures are performed and documented. 2) Male or female participants between the ages of 13 and 60 years (inclusive) at enrollment. 3) Ability to understand and follow study-related instructions. 4) Willingness to provide saliva samples for molecular analysis.

#### Exclusion criteria

1) Participants between 13 and 18 years old without the additional consent of a legal guardian. 2) Presence of pregnancy or during breastfeeding. 3) Acute infection including oral infections.

The recruitment of participants started in May 2022 and will continue until the end of 2023.

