### Study design

This is a prospective, monocentric, non-interventional observational study, which uses data collected from healthy and physically active participants in Germany **(Fig 1)**. Saliva samples will be collected by the participants themselves at home. For the analysis of potential seasonal variations, samples are grouped into a spring/summer batch and autumn/winter batch. Two rounds of saliva collection will take place between April-September 2022/2023 as spring/summer batch; and two rounds in October-March 2022/2023 (based on DST/standard time change date), as autumn/winter batch. In total four sampling rounds per person, till the end of 2023, are aimed to be collected. For each sampling round, 8 saliva samples per sampling kit, at four time points per day, should be collected during two consecutive days **(Fig 1)**.

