#### Hormonal assessment

Hormonal assessment includes quantification of melatonin, a hormone that peaks at night and promotes sleep, and cortisol, which depicts higher values in the morning contributing to increased alertness. For these measurements additional saliva samples will be collected, using home-kits from cerascreen^®^ (cerascreen GmbH, Schwerin, Germany). As indicated by the provider, for melatonin 1 ml saliva will be collected in the evening before the participant goes to bed. For cortisol analysis 7 samples with 1 ml of saliva each, distributed over the course of the day, from waking up till going to bed, will be collected. The results for hormone quantification are obtained from cerascreen^®^ in the form of a report for each participant. This information can then be used to draw a correlation between collected hormonal data and gene expression obtained from saliva samples. For each participant, sampling will be repeated at least once in Spring/Summer and once in Autumn/Winter, to determine the influence of seasonal effects. To avoid possible interference with sample collection, participants are asked not to eat or drink for 30 minutes before saliva collection. In addition, it is not recommended to brush teeth or use mouthwash before sampling to avoid these interfering with the sampling.

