### Status of the study and timeline of the study

The study started to recruit upon ethics approval, in 2022. The recruitment and data collection are planned to be carried out until the December 2023.

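### Enrolment stays open after the last spring/summer window has closed, so late recruits can give autumn/winter samples only, and the season comparison becomes partly one between different people

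*Protocol article*

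**What the plan says.** Five statements in the protocol article set the calendar.

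- Study design, spring/summer: "Two rounds of saliva collection will take place between April-September 2022/2023 as spring/summer batch".
- Study design, autumn/winter: "two rounds in October-March 2022/2023 (based on DST/standard time change date), as autumn/winter batch".
- Study design, total: "In total four sampling rounds per person, till the end of 2023, are aimed to be collected".
- Exclusion criteria, enrolment: "The recruitment of participants started in May 2022 and will continue until the end of 2023".
- Status and timeline: "The recruitment and data collection are planned to be carried out until the December 2023".

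The Hormonal assessment section is firmer than an aim: "For each participant, sampling will be repeated at least once in Spring/Summer and once in Autumn/Winter, to determine the influence of seasonal effects".

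The Sample size estimation section defines dropout narrowly: "Participants for whom there are no saliva samples collected are considered as dropout". Neither the inclusion nor the exclusion criteria mention the time a recruit has left in each season. The analysis for secondary endpoints compares seasons as subgroups with CircaCompare. It states neither pairing nor how participants seen in one season only are handled.

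**The concern.** Season is named in the aim, in the primary objective and among the secondary outcomes, and the sample size section says that 59 participants are enough for the seasonal comparison. Four rounds per person over two seasons is a layout in which each participant can serve as his or her own control. That is valuable here because the Introduction itself says that circadian rhythms vary between individuals.

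If enrolment and collection end together, the last recruits have no spring/summer window. Their samples enter only the autumn/winter side. Any difference between late and early recruits in age, sex, chronotype or activity then feeds into the apparent seasonal difference. A missed season window cannot be recovered at analysis.

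**Working it through.** **The plan's own figure.** The stated sample size is for a cosinor F-test with 2 and n − 3 degrees of freedom and noncentrality n·r²/2 (evenly spaced sampling). With r = 0.82 and α = 0.05/10 = 0.005, the smallest n with power 0.80 is 52 (power 0.8002). Inflation for 12% dropout gives 52/0.88 = 59.09, stated as 59. These figures reproduce. They concern detection of a rhythm, to which an autumn/winter-only participant still contributes, so the calendar problem does not change them.

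**Recruitment months.** May to December 2022 is 8 months and January to December 2023 is 12, which makes 20.

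**Season time left by month of enrolment**, with spring/summer taken as April to September and collection ending in December 2023:

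| Enrolled in | Spring/summer months left | Autumn/winter months left |
|---|---|---|
| May 2022 to September 2023 (17 months) | 1 or more | 3 or more |
| October 2023 | 0 | 3 |
| November 2023 | 0 | 2 |
| December 2023 | 0 | 1 |

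I counted a recruit as able to give both seasons if any calendar time remains in each, because the article states no minimum interval between rounds.

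**Effect of the season boundary.** The article also describes the cut as "based on DST/standard time change date". If the boundary is the clock change, taken here to fall in late October, most October recruits could still fit in a spring/summer round. Only November and December are then wholly lost.

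**Share affected, assuming uniform accrual:**

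- Cut at the end of September: 3/20 = 15%; 0.15 × 59 = 8.85, about 9 participants. About 50 could give both seasons.
- Cut at the clock change: 2/20 = 10%; 0.10 × 59 = 5.9, about 6 participants. About 53 could give both seasons.

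The documents give no accrual rate. For an assumed late share of 5% to 25%, the count is 0.05 × 59 = 2.95 to 0.25 × 59 = 14.75, about 3 to 15 participants.

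**What this does to an unpaired contrast.** Suppose late recruits differ from the others by δ in a rhythm characteristic and supply a share w of the autumn/winter samples. The pooled autumn/winter estimate moves by about w·δ (exact for a simple mean, approximate for phase when δ is small and amplitudes are similar). With w of 0.10 to 0.15, the season difference is displaced by about 0.10δ to 0.15δ. If late recruits give fewer autumn/winter rounds than the rest, which is likely for December enrolments, w is smaller. A within-person contrast removes this term.

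**The case against.** The best defence is that the article condenses a fuller protocol. The four rounds are worded as an aim, no paired season test is promised, and rules on evaluability usually belong in an analysis plan. Enrolment may also in practice have stopped before autumn 2023, in which case nothing is lost. The point about the aim stands for the saliva rounds. It does not cover the hormone sampling, which is stated for each participant, and it does not reconcile end dates that the article itself fixes.

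Another reading is that the autumn/winter batch ends in March 2023. Recruits from October 2023 would then have no defined round at all. The intention to collect rounds until the end of 2023 speaks against that reading, and it would make the conflict worse.

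Three stronger inferences are tempting, and the documents do not support them.

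- *The season contrast stops being within-person.* It becomes mixed. Recruits up to September 2023 can still give both seasons.
- *The late share exceeds the 12% dropout allowance.* The share is 10–15% depending on the boundary, so this is not established. The 12% also inflates N for the rhythmicity test, where not counting these people as dropouts is consistent.
- *The clock change builds a 1-hour artefact into the seasonal phase contrast.* The sample size section names Zeitgeber time as the time variable, and nowhere does the article say that uncorrected local time is used. Participants keep their normal routine. If phase follows that routine, conversion to one fixed clock would itself create a 1-hour shift. A false-positive probability for such an artefact would need 59 × 16 = 944 independent samples per season with full collection, and neither condition can be taken for granted.

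**Conclusion.** The conflict between the enrolment period and the sampling windows is real and can be read directly from the article. Participants enrolled after the last spring/summer window cannot meet the two-season schedule, and no stated eligibility or dropout rule deals with them. Under uniform accrual this concerns about 6 to 9 of 59 participants (10–15%). The true number depends on actual accrual and is zero if nobody enrols after the window closes. The consequence is partial confounding of the season comparison with time of recruitment, limited in size by the late share. The rhythmicity test and its N of 52 and 59 stand. The point is worth correcting because season is a named objective and the remedy is cheap, but it does not threaten the study as a whole.

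**What to change.** 1. Reconcile the Study design, Exclusion criteria, Hormonal assessment and timeline sections. Either set a last-enrolment date that leaves at least one spring/summer round before the autumn/winter cut, or extend collection into the next spring/summer. State whether the cut is the calendar month or the clock change.
2. Base the main season contrast on participants with at least one round in each season, analysed within person (for example, cosinor terms for season with a participant effect). Keep one-season participants in the rhythmicity analysis, and report how many there are.
3. Because the season cut may coincide with the clock change, report the seasonal phase contrast in local time and in time since recorded wake time as a sensitivity analysis. The Data management section already provides for recording exact sampling times and wake times.

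The cost is a slightly shorter enrolment window (or a longer collection period), a sentence on who is evaluable for season, and one extra analysis of data already collected.
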